### Sample size

The sample size was determined based on previous intervention studies of caregivers of PwD with the Short Sense of Competence Questionnaire (SSCQ) as an outcome measure [16, 36], using repeated measures and interaction within and between variables with a mean effect size of 0.5. In accordance with the following assumptions: alpha 0.05 and power 80%, we aim to include 102 primary caregivers (51 participants per group). Allowing for a 20% loss to follow up, we aim to enrol 122 caregivers.

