### Statistical analysis

#### Primary and secondary outcome measures

All analyses will be performed according to the intention-to-treat principle, using IBM SPSS Statistics (IBM Corp. Released 2016. IBM SPSS Statistics for Macintosh, Version 24.0. Armonk, NY: IBM Corp).

Prior to the main analysis, data will be examined for missing values, outliers and normality. To investigate whether randomisation was successful, potential differences in the baseline characteristics of the intervention and control groups will be determined using either the *t* test for the continuous variables or the chi squared (X^2^) test for the categorical variables. In the case of missing values, we will examine whether they are missing completely at random (MCAR). If the variables are MCAR, based on a comparison between the baseline characteristics of the study completers and the participants with missing values (no *P* value < .05), list-wise deletion will be applied, whereas when the missing values are not at random, we will apply a multiple imputation strategy [37].

To test the first hypothesis examining the differences in the outcome variables of the intervention group and waiting-list control group, analysis of covariance (ANCOVA) will be performed, with the outcomes of the T_2_ assessment (i.e., measured at 16 weeks, after this period the waiting-list control group can start with Inlife). The outcomes assessed at the T_2_ follow up will be included in the model as dependent variables and groups as between-subject variables. Potential baseline differences between the treatment arms will be included as covariates, if necessary. Each outcome measured will be assessed as a dependent variable in separate analyses.

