To test the changes in the primary and secondary outcome measures over the total study period, data from the intervention group and waiting-list control group will be analysed using a linear mixed model (LMM). The LMM will estimate the fixed effects of the regression slopes representing the changes during the intervals (T_0_-T_1_) and (T_1_-T_2_) in the intervention only and waiting-list control group and after the (T_2_-T_3_) follow up. This process enables a comparison of the rate of change in the caregivers who did not receive the intervention compared to the caregivers who received the intervention (T_0_-T_2_), and it provides insight into whether the potential effects on the outcome variables will be sustained by evaluating the rate of change from the 16-week follow up to the 42-week follow up (T_2_-T_3,_ intervention group only). Furthermore, LMM accounts for the fact that the data are correlated through nesting in individuals. Potential missing values are handled efficiently under the missing at random (MAR) assumption, using maximum likelihood estimates for the missing observations; hence, it is suitable for intention-to-treat analysis. Therefore, variables known to predict missing values will be included in the LMM analyses [38]. Intervals will be entered as categorical variables, using three dummies. The best model fit of the models with random intercept (at the participant level) and with random intercept and random slope (at interval level) will be compared with likelihood ratio tests. All tests will be two-tailed, with an alpha level of 0.05.

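### The stated repeated-measures basis does not reproduce 102 caregivers at 80% power; a two-tailed T2 comparison without guaranteed baseline adjustment has about 71% power

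*Protocol article*

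**What the plan says.** The Sample size section of the protocol article takes its effect size from earlier caregiver trials that used the SSCQ. It describes the calculation as "using repeated measures and interaction within and between variables with a mean effect size of 0.5". It then gives the result: "In accordance with the following assumptions: alpha 0.05 and power 80%, we aim to include 102 primary caregivers (51 participants per group". It does not give the sidedness of alpha, the effect-size metric (d or f), the number of measurements or a within-person correlation.

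The Statistical analysis section, under Primary and secondary outcome measures, tests the first hypothesis by ANCOVA on the 16-week outcome: "The outcomes assessed at the T_2_ follow up will be included in the model as dependent variables and groups as between-subject variables". Baseline differences between the arms become covariates only if this is judged necessary. The same section later plans a linear mixed model over the whole study period and closes with "All tests will be two-tailed, with an alpha level of 0.05".

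**The concern.** A sample size should follow from its stated inputs and should refer to the test that decides the primary question. Here the described basis is an interaction over repeated measurements, whereas the first hypothesis is tested at a single time point. The number is also much smaller than the familiar two-sided answer for a standardised difference of 0.5.

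What is at stake is how a null result is read. If the T2 comparison has about 71% power at d = 0.5, the chance of missing such an effect is about 29%, yet readers would take the trial as having a 20% miss rate. The type I error and the effect estimates are not affected.

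**Working it through.** **Inputs from the protocol.** Effect size 0.5, alpha 0.05, power 80%, 51 per group (102 in total), from Sample size. Two-tailed tests and a T2 ANCOVA with conditional covariates, from Statistical analysis.

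**Assumptions, because the protocol is silent.** The effect size is d = 0.5, or f = 0.25 or 0.5 in the repeated-measures formulas. There are 2 to 4 measurements (m). The correlations (rho, r) are shown as ranges.

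**1. Can 102 be reproduced?** For a two-sample t-test the noncentrality is d·√(n/2) on 2n − 2 degrees of freedom. At n = 51 this is 0.5 × √25.5 = 2.525.

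| Test | n per group | Power |
|---|---|---|
| One-sided 0.05 | 50 | 79.9% |
| One-sided 0.05 | 51 | 80.6% |
| Two-sided 0.05 | 51 | 70.6% |
| Two-sided 0.05 | 63 | 79.5% |
| Two-sided 0.05 | 64 | 80.1% |

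So 51 is the smallest one-sided n that reaches 80%. The two-sided answer is 64 per group, or 128 in total. With 51 per group, the two-sided effect detectable at 80% power is d ≈ 0.56.

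**2. Does the described interaction give 102?** The usual within-between formula has λ = f²·N·m/(1 − rho), with degrees of freedom m − 1 and (N − 2)(m − 1). Total N for 80% power, over m = 2 to 4 and rho = 0 to 0.8:

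- f = 0.25 (equivalent to d = 0.5): 12 to 66.
- f = 0.5: 6 to 18.

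At N = 102 and f = 0.25 this formula gives at least 94% power throughout. A second convention defines f on the interaction itself, with λ = f²·N·(m − 1). It gives 128, 80 and 60 at f = 0.25, and 34, 22 and 16 at f = 0.5, for m = 2, 3 and 4. None of these is 102.

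**3. Do other two-sided routes come near 102?** Yes, but each needs a correlation that the protocol does not state:

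- Between-group factor of a repeated-measures ANOVA, λ = f²·N·m/(1 + (m − 1)·rho), f = 0.25: 102 at m = 2, rho = 0.58; 104 at m = 2, rho = 0.6, at m = 3, rho = 0.7, and at m = 4, rho = 0.75.
- Change score at r = 0.6: 104.
- ANCOVA on the baseline score at r = 0.45: 104, with 80.0% power at 102.

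**4. Power of the planned T2 test with 51 per group, two-sided.** Adjustment for a baseline score with correlation r raises the effective difference to 0.5/√(1 − r²).

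| Assumed r | Effective d | Power |
|---|---|---|
| no adjustment | 0.500 | 70.6% |
| 0.3 | 0.524 | 74.6% |
| 0.4 | 0.546 | 77.9% |
| 0.45 | 0.560 | 80.0% |
| 0.5 | 0.577 | 82.3% |
| 0.6 | 0.625 | 87.8% |

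Taking one further degree of freedom for the covariate changes these powers by less than 0.1 percentage point.

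**The case against.** A reader might infer that the authors ran a one-sided t-test by mistake. The documents do not support that. The section names neither a t-test nor a one-sided alpha, and step 3 shows that two-sided routes also land on or near 102 at plausible correlations. The exact match with the one-sided result is suggestive but does not establish the cause.

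A reader might also infer that the trial's power simply is 71%. That too goes further than the text. The planned test is an ANCOVA, and if the baseline score is in the model with a correlation of about 0.45 or more, two-sided power is 80% or better. What stands against this defence is that the protocol does not guarantee the covariate, so the unadjusted figure is the only one that it secures.

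Three further points are fair:

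- An article may leave the metric, visits and correlation to the full protocol, and the source trials for the 0.5 are not at hand. One can therefore say that 102 does not follow from what is shown, but not why.
- The interaction ranges in step 2 depend on convention, although neither convention tried gives 102.
- A repeated-measures basis is not foreign to the plan, since a mixed model is planned on the same outcomes. The mismatch is specifically with the T2 ANCOVA.

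**Conclusion.** The point holds in a limited form. The sample-size statement cannot be reproduced from its described basis under the usual formula, and that basis is not the test of the first hypothesis.

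With two-tailed testing at 0.05, d = 0.5 and 51 analysed per group, the power secured by the plan as written is about 71%, roughly nine percentage points below the stated 80%. This rests on reading 0.5 as a standardised mean difference at T2 and on no baseline covariate. With the baseline score always included, the claim of 80% becomes true at a baseline-T2 correlation of about 0.45 or higher. The documents give no value for that correlation, so the result is a range and not a single figure. How 102 was actually derived remains unknown.

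**What to change.** Rewrite the sample-size paragraph for the analysis that tests the first hypothesis:

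- State two-sided alpha 0.05 and the T2 ANCOVA as the test.
- Name the effect size as d = 0.5.
- Prespecify the baseline value of each outcome as a covariate, in place of the conditional wording in Statistical analysis.
- Give the assumed baseline-T2 correlation with its justification, and report the power at 51 per group together with the range (71% without adjustment, 82% at r = 0.5).
- Remove the repeated-measures interaction as the basis for 102.

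Planned enrolment can stay as it is. The cost is a change of text and a stated power that may be less favourable, since 80% then depends on a correlation of about 0.45 or more.

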**Methods:**

A mixed-method, randomised controlled trial with 122 caregivers of PwD will be conducted. Participants will be assigned to either the Inlife social support intervention or a waiting-list control group. After 16 weeks, the control group will obtain access to the Inlife environment. Data will be collected at baseline (T_0_) and at 8-week (T_1_), 16-week (T_2_) and 42-week follow up (T_3_). The 16-week follow-up assessment (T_2_) is the primary endpoint to evaluate the results on the primary and secondary outcomes, measured by self-reported questionnaires. The primary outcomes include feelings of caregiver competence and perceived social support. The secondary outcomes include received support, feelings of loneliness, psychological complaints (e.g., anxiety, stress), and quality of life. A process evaluation, including semi-structured interviews, will be conducted to examine the internal and external validity of the intervention.

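### Enrolling 122 caregivers does not preserve the required 102 after a 20% loss: it leaves about 98 (wrong as written, low severity)

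*Protocol article*

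**What the plan says.** The Sample size section bases its target on earlier caregiver trials that used the SSCQ, "using repeated measures and interaction within and between variables with a mean effect size of 0.5". With alpha at 0.05 and power at 80%, it concludes: "we aim to include 102 primary caregivers (51 participants per group"). The next sentence sets the enrolment: "Allowing for a 20% loss to follow up, we aim to enrol 122 caregivers". The Methods paragraph of the abstract gives the same total as the size of the trial: "A mixed-method, randomised controlled trial with 122 caregivers of PwD will be conducted".

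The article does not show how it got from 102 to 122. It does not define the 20% as anything other than a loss to follow-up, and it gives no other reason for 122.

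The statistical section bears on how a lost caregiver is treated. The group comparison at 16 weeks (T2) is an ANCOVA. Missing values lead to list-wise deletion if they are judged to be missing completely at random, and to multiple imputation otherwise. A linear mixed model over all visits uses partial data under missing at random. On sidedness it says: "All tests will be two-tailed, with an alpha level of 0.05".

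**The concern.** A dropout allowance has one purpose: to make sure that the number left at the end is the number the power statement needs. Loss to follow-up is ordinarily a share of those enrolled, so the required number is divided by the fraction retained. The step from 102 to 122 looks instead like adding 20% of 102 on top, which is always too small.

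If so, the enrolment target does not deliver the sample behind the stated 80% power, even when retention is exactly as the plan expects. A reader would also believe that the design tolerates more dropout than it does.

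**Working it through.** **Inputs, all from the Sample size section:** 102 needed (51 per group); 20% loss; 122 enrolled; effect size 0.5; alpha 0.05; power 80%. Two-sided testing comes from the statistical section. I read the 20% as a share of those enrolled and apply it at T2, the primary endpoint.

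**1. Reproducing the plan's figure.** 102 × (1 + 0.20) = 122.4, which rounds to 122. The formula is inferred. The next two steps do not depend on it.

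**2. What 122 delivers.**
- Completers at 20% loss: 122 × (1 − 0.20) = 97.6, about 98.
- Per group: 61 × 0.8 = 48.8, about 49.
- Shortfall: 102 − 97.6 = 4.4, so 4 to 5 caregivers.
- Loss that 122 can absorb: 1 − 102/122 = 20/122 = 16.4%.

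**3. What 102 completers would need.** 102/(1 − 0.20) = 127.5, rounded up to 128 (64 per group). Check: 128 × 0.8 = 102.4. The difference from 122 is 6 caregivers, so rounding does not explain it.

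**4. Cost in power.** I used the two-sample t-test with noncentrality d × √(n/2), n per group and 2n − 2 degrees of freedom. The repeated-measures calculation itself cannot be rebuilt, because the article gives no within-person correlation. The table therefore shows the change from 51 to 49 per group on several bases.

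| Basis | 51 per group | 49 per group | Change (points) |
|---|---|---|---|
| Two-sided, d = 0.56 (the value at which 51 per group gives 80%) | 80.0% | 78.4% | −1.6 |
| Two-sided, unadjusted, d = 0.5 | 70.6% | 68.8% | −1.8 |
| One-sided, unadjusted, d = 0.5 | 80.6% | 79.2% | −1.4 |
| Two-sided ANCOVA, d = 0.5, assumed baseline correlation 0.4 | 77.9% | 76.2% | −1.7 |
| Same, assumed correlation 0.5 | 82.3% | 80.8% | −1.5 |
| Same, assumed correlation 0.6 | 87.8% | 86.5% | −1.3 |

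The correlations are my assumptions. The level of power depends heavily on the basis chosen. The change due to the allowance does not: it is 1.3 to 1.8 points throughout.

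**The case against.** **The practical effect is small, and some of it may not occur.** This stands. List-wise deletion applies only if missing values are judged completely at random; otherwise they are multiply imputed, and the mixed model keeps partial records. A caregiver lost before T2 is therefore not always wholly lost to analysis. That softens the consequence but does not make 122 yield 102 completers.

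**The 20% could be meant as a share of the 102.** On that reading, adding 20 caregivers to 102 is about right (20/102 = 19.6%). Nothing in the article says so, and a loss to follow-up would not normally be understood that way.

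**A reader might infer that the trial has only about 69% power, because 102 came from a one-sided calculation.** It is true that 51 per group matches a one-sided t-test at d = 0.5, and that an unadjusted two-sided test would need 64 per group. The article does not establish this as the source, however. It describes a repeated-measures calculation with an unstated correlation, and a two-sided ANCOVA with a baseline correlation of about 0.45 would also give 51 per group. Even on the unadjusted two-sided basis, power is already 70.6% at 51 per group, so only 1.8 points belong to the dropout allowance. The basis of the 102 is a separate question.

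**A reader might instead take comfort from baseline adjustment.** The statistical section does not commit to it: baseline differences between arms enter the ANCOVA as covariates only where judged necessary. The ANCOVA rows above illustrate a possible analysis, not a fixed one.

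**Conclusion.** The Sample size section is wrong as written. A requirement of 102, a 20% loss and an enrolment of 122 cannot all hold. At the plan's own loss rate about 98 caregivers remain, 49 per group, and 122 covers about 16% loss. This follows from the stated figures and needs only the ordinary reading of the 20% as a share of those enrolled.

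Severity is low. The slip costs about 1 to 2 points of power: about 78% instead of 80%, if 51 per group does give 80%. It bears most on the T2 ANCOVA under list-wise deletion. No estimand, analysis method or conclusion changes. The finding does not show that the trial is seriously underpowered or that the 102 itself is wrong.

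**What to change.** Restate the sentence in the Sample size section in one of two ways:

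- *An enrolment of 122 allows for about 16% loss to follow-up*; or
- *An enrolment of 122 with 20% loss leaves about 98 analysed (49 per group)*, followed by the two-sided power at 49 per group for the analysis actually planned. State the assumptions, including any correlation and whether the baseline score is a covariate.

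Either is a wording change. The cost is a slightly less favourable retention tolerance or power figure, and the 122 in the abstract can stay.

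If the sponsor wants 102 completers at 20% loss, the matching enrolment is 128, six more caregivers, and the abstract must change too. The Trial status section says recruitment was still under way, so this was possible when the article was written, but the correction does not require it.

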### Statistical analysis

#### Primary and secondary outcome measures

All analyses will be performed according to the intention-to-treat principle, using IBM SPSS Statistics (IBM Corp. Released 2016. IBM SPSS Statistics for Macintosh, Version 24.0. Armonk, NY: IBM Corp).

Prior to the main analysis, data will be examined for missing values, outliers and normality. To investigate whether randomisation was successful, potential differences in the baseline characteristics of the intervention and control groups will be determined using either the *t* test for the continuous variables or the chi squared (X^2^) test for the categorical variables. In the case of missing values, we will examine whether they are missing completely at random (MCAR). If the variables are MCAR, based on a comparison between the baseline characteristics of the study completers and the participants with missing values (no *P* value < .05), list-wise deletion will be applied, whereas when the missing values are not at random, we will apply a multiple imputation strategy [37].

To test the first hypothesis examining the differences in the outcome variables of the intervention group and waiting-list control group, analysis of covariance (ANCOVA) will be performed, with the outcomes of the T_2_ assessment (i.e., measured at 16 weeks, after this period the waiting-list control group can start with Inlife). The outcomes assessed at the T_2_ follow up will be included in the model as dependent variables and groups as between-subject variables. Potential baseline differences between the treatment arms will be included as covariates, if necessary. Each outcome measured will be assessed as a dependent variable in separate analyses.

To test the changes in the primary and secondary outcome measures over the total study period, data from the intervention group and waiting-list control group will be analysed using a linear mixed model (LMM). The LMM will estimate the fixed effects of the regression slopes representing the changes during the intervals (T_0_-T_1_) and (T_1_-T_2_) in the intervention only and waiting-list control group and after the (T_2_-T_3_) follow up. This process enables a comparison of the rate of change in the caregivers who did not receive the intervention compared to the caregivers who received the intervention (T_0_-T_2_), and it provides insight into whether the potential effects on the outcome variables will be sustained by evaluating the rate of change from the 16-week follow up to the 42-week follow up (T_2_-T_3,_ intervention group only). Furthermore, LMM accounts for the fact that the data are correlated through nesting in individuals. Potential missing values are handled efficiently under the missing at random (MAR) assumption, using maximum likelihood estimates for the missing observations; hence, it is suitable for intention-to-treat analysis. Therefore, variables known to predict missing values will be included in the LMM analyses [38]. Intervals will be entered as categorical variables, using three dummies. The best model fit of the models with random intercept (at the participant level) and with random intercept and random slope (at interval level) will be compared with likelihood ratio tests. All tests will be two-tailed, with an alpha level of 0.05.

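### A non-significant baseline comparison is allowed to declare the data missing completely at random and so to drop randomised caregivers from the T2 ANCOVA

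*Protocol article*

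**What the plan says.** The rule stands in the protocol article under *Statistical analysis*, *Primary and secondary outcome measures*.

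- The section opens with a general commitment: "All analyses will be performed according to the intention-to-treat principle".
- MCAR is judged "based on a comparison between the baseline characteristics of the study completers and the participants with missing values". The criterion for accepting it is that no P value falls below .05.
- If the criterion is met, "list-wise deletion will be applied, whereas when the missing values are not at random, we will apply a multiple imputation strategy".
- The first hypothesis is then tested: "analysis of covariance (ANCOVA) will be performed, with the outcomes of the T_2_ assessment". *Methods/design* names T2 (16 weeks) as the primary endpoint.
- Baseline enters that model only conditionally: "Potential baseline differences between the treatment arms will be included as covariates, if necessary".
- For the linear mixed model (LMM) of change over the whole study, the same section takes another approach: "Potential missing values are handled efficiently under the missing at random (MAR) assumption". It uses maximum likelihood, includes predictors of missingness, and calls this suitable for intention-to-treat.

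**The concern.** The step from a non-significant comparison to MCAR is not valid. MCAR means that missingness is unrelated to anything, observed or unobserved. A comparison of baseline characteristics can contradict that but cannot establish it. Three kinds of dropout can pass the test:

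- dropout that depends on T1 scores or on experience with the platform;
- dropout that depends on the T2 score that was never observed;
- dropout that runs in opposite directions in the two arms, because the comparison as described pools the arms.

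Arm-specific dropout is plausible here, since before T2 only one arm uses the platform.

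Passing the test removes randomised caregivers from the comparison at the primary endpoint. Their T1 scores, which could inform the missing T2 values, go unused. At stake are the between-group estimates for caregiver competence and perceived social support, and the consistency of the plan with its own intention-to-treat statement.

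**Working it through.** **1. Size of the comparison.** *Sample size* gives 102 analysed, 20% loss and 122 enrolled. The enrolment figure is reproduced by 102 × 1.2 = 122.4. Twenty per cent of 122 is 24.4, so I take 24 missing and 122 − 24 = 98 complete. The split is an assumption built on the planned loss.

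**2. Power of the test for one baseline variable.** For a two-sided t test at 0.05, the noncentrality is d × √(n₁n₀/(n₁+n₀)) = d × √(24 × 98/122) = d × 4.39. There are 120 degrees of freedom and the critical value is 1.98.

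- d = 0.3: noncentrality 1.32, power 26%.
- d = 0.5: noncentrality 2.20, power 59%.
- 80% power needs d of about 0.64.
- With other amounts of missing data, power at d = 0.5 is 37% (12 missing) and 71% (37 missing).

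These figures are for one variable. The rule leaves the MCAR branch if any variable reaches P < .05, so they are not the power of the whole screen.

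**3. Chance in the choice of method.** With k independent tests under true MCAR, the probability of at least one P < .05 is 1 − 0.95^k: 23% for k = 5, 40% for k = 10 and 46% for k = 12. *Demographics* lists about 12 characteristics, but the article does not say which are tested. Chance therefore plays a large part in which method is used.

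**4. Effect on the estimate, dropout driven by T1.** Every mechanism in steps 4 and 5 is an assumption; the article gives no dropout model. The setting is 61 per arm, no true effect, correlations of 0.6, and intervention caregivers with poor change by T1 more likely to leave, giving 19% v 12% loss (11.6 + 7.3, about 19 caregivers).

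- List-wise estimate with baseline adjustment: bias about 0.04 to 0.06 SD over repeated simulations, in favour of the intervention.
- Analysis using T1 under MAR: bias about 0.00.
- A screen of ten baseline variables declared MCAR in about half the runs (50% to 53%).

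On type I error, the standard error is √(1 − 0.6²) × √(1/49.4 + 1/53.7) = 0.158. A bias of 0.056 is then 0.056/0.158 = 0.35 standard errors, and Φ(−1.96 + 0.35) + Φ(−1.96 − 0.35) is about 6.5%. A bias of 0.04 gives about 5.7%. Hence about 6% against a nominal 5%.

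**5. Effect on the estimate, other mechanisms.** These also assume no true effect. They screen one baseline variable, use a logistic slope of 1 per SD and a T0–T1 correlation of 0.5, and give results among trials that pass the screen.

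- Dropout depends on baseline, in opposite directions by arm: passes 94%; unadjusted bias 0.21 SD, type I error 18%; adjusted bias 0.
- Dropout in one arm depends on T1: passes 83%; unadjusted bias 0.13 SD, type I error 10%; adjusted bias 0.08 SD.
- Dropout in one arm depends on the T2 outcome: passes 80%; unadjusted bias 0.18 SD, type I error 15%; adjusted bias 0.13 SD.
- Dropout in one arm depends on baseline: passes only 48%, since the screen can see it; unadjusted bias 0.11 SD, adjusted bias 0.
- True MCAR: bias 0.

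The unadjusted figures are relevant because the plan adjusts for baseline only where it judges this necessary.

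**6. The two rules side by side.** In one section, the T2 ANCOVA may discard caregivers after a pretest, while the LMM, whose T0–T2 part covers the same groups and period, keeps them under MAR. The approach the article itself describes as suitable for intention-to-treat is not the one attached to the test at the primary endpoint.

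**The case against.** The case for leaving the plan alone has several parts.

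- **The LMM is a safeguard.** It covers T0 to T2 under MAR and uses T1, so a sounder result will stand beside the ANCOVA. This holds in part. Having two analyses with different purposes and assumptions is not an error in itself. But the article gives the first hypothesis to the ANCOVA and presents the LMM as a test of change over the study, so the weaker rule governs the T2 comparison.
- **Complete-case ANCOVA does not need MCAR.** If dropout depends only on arm and on covariates in the model, the adjusted complete-case estimate is unbiased, as two of the mechanisms above show. This is correct. It does not help when dropout depends on T1, or when baseline is left out of the model.
- **The harm is small and hypothetical.** In the T1-change scenario it is, and no mechanism is documented. The larger figures rest on assumed slopes and mostly on unadjusted comparisons. This stands and limits the severity.

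A reader might also infer three stronger points that the article does not support.

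- **That multiple imputation is reserved for a mechanism it cannot handle.** Read literally, values not at random would be outside standard imputation, which assumes MAR. But that branch is entered when observed baseline characteristics do differ, a situation MAR can cover. The natural reading is not completely at random, which makes this a wording error.
- **That the 40% chance of falsely rejecting MCAR is a harm.** That error leads to imputation, which remains valid under MCAR. It is the safe direction.
- **That a missing not-at-random sensitivity analysis is a defect.** Such detail may be left to the statistical analysis plan, which is not shown.

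**Conclusion.** The point holds: a baseline comparison without significance should not select list-wise deletion for the T2 ANCOVA under a declared intention-to-treat principle. The rule is stated in full and badly fixed, so this is not a matter of omitted detail. That the test cannot see post-baseline dropout follows from its design and needs no simulation.

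The size does rest on assumptions. Bias is about 0.04 to 0.06 SD with type I error about 6% when intervention-arm dropout follows T1 change and baseline is adjusted for. It is 0.13 to 0.21 SD, with type I error 10% to 18%, under three other mechanisms without baseline adjustment. If the planning effect of 0.5 is read in SD units (the article does not state the metric), these are 0.04/0.5 to 0.06/0.5 = 8% to 12% and 0.13/0.5 to 0.21/0.5 = 26% to 42% of it. Nothing in the article shows that such dropout will occur, so a claim that the result will be seriously biased goes too far. Severity: should be fixed.

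**What to change.** Delete the MCAR pretest and the list-wise deletion branch. Name one MAR-based analysis of all randomised caregivers for the T2 comparison, chosen before outcome data are examined. Either of these would serve:

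- the group contrast at T2 from the LMM already planned, fitted by maximum likelihood to T0, T1 and T2; or
- ANCOVA at T2 after multiple imputation, with an imputation model that always includes T0, T1, arm and predictors of dropout.

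If imputation is kept, correct the wording to not completely at random if that is what is meant, and state that the imputation assumes MAR.

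The change deals with dropout that depends on observed data, including T1. It does not remove bias from dropout that depends on the unobserved T2 score; how to examine that can be settled in the statistical analysis plan.

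The cost is revised wording and a little more analysis work. All the data needed are already scheduled for collection.
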